
### Adverse events

All adverse events, defined as any negative or unwanted reactions to intervention, will be recorded through the symptoms reported by the patients, and observations by a researcher at every visit. Therapeutic US may cause mild local swelling, spot-like bleeding, ecchymosis, enhanced local pain response and local hyperesthesia or decrease. Night splint may cause skin allergy, wrist stiffness, etc. The participants will be instructed to do gentle range-of-motion exercises when removing the splint to prevent stiffness and reinforced adherence by verbal instruction.

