**Trial registration number:**

ChiCTR2100050701.

Strengths and limitations of this studyTherapeutic ultrasound as independent or adjunct therapy in treating carpal tunnel syndrome (CTS).The first randomised controlled trial (RCT) to compared the efficacy between therapeutic ultrasound and night splint in CTS treatment.Multicentre RCT with blinded outcome assessor and statistician.Use of several patient-reported outcome measures as well as objective parameters.Participants and treating surgeons not blinded.

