### Intervention

At the beginning, all participants will participate in an about 30 min group educational presentation by a research assistant on the same day as the baseline assessment. This presentation will cover the pathophysiology, treatment options, posture and activity modification principles of CTS. The above information will also be provided to participants in the form of education booklets, to encourage them to review at home. Habits changes include limited wrist movement and a reduction in strenuous work activities, and the use of ergonomically friendly work tools helps reduce median nerve pressure.^32 33^

Participants in the (therapeutic US group) will receive pulsed therapeutic US (model 1:4, Shanghai, China) for 6 weeks at a frequency of 1 MHz and intensity of 1.0 W/cm^2^ for 15 min per session, in daily five times a week for the first 2 weeks and twice a week for another 4 weeks, to the area over the carpal tunnel, referred to a published trial (BMJ. 1998;316:731–735).

Participants allocated to the (night splint group) will receive a splint to wear at night for 6 weeks, referred to a published trial (Lancet. 2018;392:1423–1433). The splint holds the wrist in a neutral position or slightly extended 20° from the neutral position to avoid wrist movement, which can increase pressure on the carpal tunnel.^34^ The choose of each splint will be based on the size of individual participant’s hands and arms. Participants will be shown how to fit and remove the wrist splint according to a standardised trial protocol. Oral guidance from the clinician on how and when to use splints will encourage and reinforce compliance, which will be also supported by written information, detailed care and splint fitting and use. Participants will be instructed to perform gentle range-of-motion exercises when removing the splint to prevent stiffness.

Participants randomised to the (therapeutic US+night splint group) will receive both therapeutic US for 6 weeks as in the (therapeutic US group) and night splint for 6 weeks as in the (night splint group).

For participants with bilateral CTS, the non-study hand will be treated according to normal clinical protocols in use at the research site.

We discouraged additional treatments to that assigned (ie, not per protocol) during the intervention period, but we allowed the use of simple analgesics as needed. Participants reported all not per protocol treatments, such as drugs, in a diary.

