### Data management

Data will be collected during the participants’ visits to the hospital at baseline, 6 weeks, 3 months, 6 months and 1 year after random assignment (table 1). Reminder emails and phone calls from the research assistants will be programmed to maximise participant compliance in subsequent completion. A registered participant will withdraw from the study if (1) the participant withdraws his/her consent and (2) exclusion criteria is found after registration. The cause and date of suspension will be recorded. Consent to use data that has been collected before the participant’s withdrawal will be included in the consent form.

**Table 1 T1:** Study evaluation procedures and timeline

Study procedure	Medical evaluation	Enrolment visit	6 weeks	3 months	6 months	1 year
Determine eligibility	√	√				
Obtain signed consent		√				
Obtain medical and demographic data		√				
Give instructions for pain medication diary		√				
Outcome measures						
Boston Carpal Tunnel Questionnaire		√	√	√	√	√
Interrupted Sleep Questionnaire		√	√	√	√	√
European Quality of Life Scale (EuroQol)-5D		√	√	√	√	√
Hospital Anxiety and Depression Scale		√	√	√	√	√
Work Limitations Questionnaire-25		√	√	√	√	√
Treatment success rate			√	√	√	√
Treatment recurrence rate				√	√	√
Physical examination		√	√	√	√	√
Electrophysiological and ultrasound parameters		√	√	√	√	√

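### The adverse event definition makes attribution to treatment a condition for recording, so unexpected or unattributed events can be lost and the same symptom may be recorded differently by arm

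*Protocol article*

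**What the plan says.** The Adverse events section covers all adverse events, "defined as any negative or unwanted reactions to intervention". These "will be recorded through the symptoms reported by the patients, and observations by a researcher at every visit". The section then gives expected reactions by treatment. For ultrasound they are swelling, small bleeds, bruising, more local pain, and heightened or reduced local sensation. For the splint they are skin allergy and stiffness of the wrist, with the list left open-ended.

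On blinding, the strengths and limitations list states: "Participants and treating surgeons not blinded". The Randomisation and blinding section blinds the outcome assessor and the statistician. The researcher who observes adverse events is not identified with any of these roles.

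The Data management section places data collection at "visits to the hospital at baseline, 6 weeks, 3 months, 6 months and 1 year after random assignment", the same for all arms.

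**The concern.** An adverse event is normally any untoward occurrence, and whether treatment caused it is a separate, later judgement. Here the causal judgement comes first and decides whether anything is written down. An event that nobody links to treatment at the time falls outside the definition and cannot be recovered at analysis. Unexpected harms are the most exposed, because nobody is looking for a link.

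The filter may also differ by arm. Participants know what they received, and the stated expectations differ by treatment. A count of events by arm would then partly reflect what people expected each treatment to do. The Discussion names safety among the attractions of ultrasound and foresees offering it to selected patients if it proves effective, so the harms record should be able to stand on its own.

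**Working it through.** The article gives no adverse event figure to reproduce, so the check sets its statements side by side.

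**1. What the definition admits.** Three kinds of event after randomisation can be tested against the wording in "defined as any negative or unwanted reactions to intervention":

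- An untoward event linked to treatment is recorded.
- An untoward event with no link made at the time is not required to be recorded.
- An untoward event of a kind not expected from either treatment is recorded only if someone nevertheless suspects treatment.

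The rule says all adverse events, but its definition reaches only the first kind reliably.

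**2. Who makes the link.** There are two sources, participants' symptom reports and a researcher's observation.

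- Participants are unblinded, so any attribution on their side is made knowing the arm.
- The researcher's role is not specified. If that person knows the arm, the attribution is unblinded. If that person is the blinded outcome assessor, deciding whether something is a reaction to the intervention invites guessing or learning the intervention, which puts the blind at risk. Recording the event without a causal condition avoids both problems.

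**3. Whether the expectation lists treat the same symptom alike.** The inclusion criteria grade carpal tunnel syndrome by paraesthesia, numbness, pain and sensory loss.

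| Symptom during follow-up | On the ultrasound list | On the splint list | Also a feature of the disease |
|---|---|---|---|
| More local pain | Yes | Not named | Yes |
| Altered or reduced sensation | Yes | Not named | Yes |
| Skin allergy | Not named | Yes | No |
| Wrist stiffness | Not named | Yes | No |

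The first two rows carry the problem. More pain or numbness matches a listed reaction in the ultrasound and combined arms. In the splint arm it is more easily read as the disease and left out. This does not depend on how often each arm is seen.

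**4. What other measurements recover.** The Boston questionnaire, the physical examination and the electrophysiology are scheduled at baseline and at all four follow-up visits in every arm. The global rating of change, whose categories include two for worsening, is collected at the four follow-up visits. Deterioration of carpal tunnel symptoms is therefore captured as an outcome even if it is not recorded as an adverse event. What those measures do not capture is an untoward event outside their scope that nobody attributed to treatment.

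**5. Size.** To quantify the loss one would need the true event rate in each arm and the proportion attributed to treatment in each arm. The article gives neither, so no figure is offered.

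**The case against.** The strongest reply has four parts.

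- **This is a condensed article.** The Quality assurance section refers to a manual of operations and a case report form, neither of which is shown. Fields for relatedness and seriousness and a standard set of questions commonly sit there. This stands: their absence from the article is no finding. The definition, however, is stated in the article, and it is the statement that is at fault.
- **Worsening is measured anyway, and the splint list is not closed.** Both are true and narrow the point, as step 4 shows. They do not help with unexpected events, and an open-ended list still does not name pain or altered sensation for the splint.
- **Staff attribution is not shown to be unblinded.** Correct. Only the participants' side is established as unblinded; the researcher's role is simply not given.
- **No between-arm safety analysis is specified.** Also correct. Adverse events are not among the listed outcomes, have no row in Table 1, and do not appear in the Analysis plan.

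A reader might go further and infer that ultrasound participants have many more chances to have an event recorded. Ultrasound is given "in daily five times a week for the first 2 weeks and twice a week for another 4 weeks", which is 5 × 2 + 2 × 4 = 18 sessions in each of the two ultrasound-containing arms, and none is described for the splint arm. The documents do not support building on this. Events are noted through "observations by a researcher at every visit", and the Data management section uses visits for the scheduled assessments, four after baseline in every arm. The Intervention section speaks of sessions. On that vocabulary the opportunities are equal. Even if sessions counted, a recorded ratio under equal true risk would be 1/q, with q an assumed detection rate in the splint arm relative to the ultrasound arms. It would only restate the assumption.

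**Conclusion.** The point holds for the definition. As worded, the rule records adverse reactions rather than adverse events, with attribution resting partly on unblinded participants and guided by different expectations for each treatment. Unexpected or unattributed events can go unrecorded, and increased pain or altered sensation may be handled differently by arm. The size, and the net direction, of any resulting bias cannot be derived from the article.

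The conclusion assumes that staff will follow the definition as written. If the case report form already collects every untoward event, the practical loss is smaller, and the article's wording should be brought into line with it.

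Two stronger conclusions should not be drawn. The article does not establish unequal ascertainment from ultrasound sessions, so it cannot be said that a safety comparison between arms is unreliable; no such comparison is specified. Nor does the Discussion claim that ultrasound is safer than splinting: its remark compares ultrasound with other non-operative therapy such as drug injections, and no injection arm exists here.

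**What to change.** - Define an adverse event as any untoward occurrence after randomisation, whatever its presumed cause, including worsening of carpal tunnel symptoms.
- Record relatedness and seriousness as separate fields, after the event itself has been recorded, and say who judges relatedness. If the blinded outcome assessor collects events, someone else should make that judgement.
- Keep the expected reactions as information only, not as a guide to what qualifies.
- Ask the same questions in all three arms at 6 weeks, 3 months, 6 months and 1 year, and base any tabulation by arm on these answers.
- State that the visits meant in the Adverse events section are these scheduled ones, and list any events noted at ultrasound sessions separately.

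The cost is a change of wording and, if not already present, one or two case report form fields. Treatment, sample size and visit schedule are untouched. The downside is that more unrelated events will be recorded and will have to be reviewed.

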### Sample size calculation

Sample size and power calculation are based on the primary outcome of BCTQ-SSS score at 6 weeks. All sample size calculations assume two-sided analysis with a power of 90% (1-β=0.90) at a significant level of α=0.05. Based on a published RCT trial (Lancet. 2018;392:1423–1433), the authors compared corticosteroid injection and night splint for CTS, and participants in the night splint group had an SD (SD) of 0.76 points for BCTQ-SSS at their 6-week follow-up, (‘6 weeks’ was the primary endpoint in this study)),^9^ an SD of 0.76-point on BCTQ-SSS score will be used. To detect a minimum clinically significant difference of 0.8-point^53^ (superiority margin) between therapeutic US+night splint and night splint groups (assuming a true difference of 1.19-point,^9 54^ a total of 48 participants in each group is required. Allowing for an up to 10% drop-out rate, we aim to enrol at least 54 participants in each group to complete the study.

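### 48 per group does not give the stated 90% power at two-sided 0.05: on the protocol's own inputs power is about 70%, and 48 is the figure for 80% power one-sided

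*Protocol article*

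**What the plan says.** The whole calculation is in one paragraph of the protocol article, under Sample size calculation. The error rates are set first: "All sample size calculations assume two-sided analysis with a power of 90% (1-β=0.90) at a significant level of α=0.05". The SD comes from the night-splint arm of an earlier trial at 6 weeks: "an SD of 0.76-point on BCTQ-SSS score will be used". The target is a "minimum clinically significant difference of 0.8-point^53^ (superiority margin"), to be shown "between therapeutic US+night splint and night splint groups", "assuming a true difference of 1.19-point". The conclusion is that "a total of 48 participants in each group is required". This is raised to 54 per group for up to 10% drop-out, and the abstract gives the total as 162.

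Allocation is 1:1:1 (Randomisation and blinding). The Analysis plan says the primary comparison will use linear regression. It names no margin there and ties its covariate list to the secondary mixed model. The article gives no baseline correlation or adjusted SD.

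**The concern.** A margin of 0.8 together with a separate, larger true difference of 1.19 describes a test of superiority by a margin. The effect that drives such a calculation is the excess over the margin, 0.39 points, or about half an SD (0.39 / 0.76 = 0.51). For an effect of that size, 48 per group is visibly too few for 90% power at two-sided 0.05.

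This paragraph is the only power justification in the article. If the primary result is not significant, readers will judge it against a claimed 10% false-negative risk. The Discussion describes earlier studies of adding ultrasound to splinting as conflicting, so an overstated power could lead readers to take an inconclusive result as evidence that ultrasound adds nothing.

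**Working it through.** **Inputs** (all from Sample size calculation, except allocation)
- SD 0.76
- margin 0.8; true difference 1.19; excess over margin 1.19 − 0.8 = 0.39
- alpha 0.05, two-sided; power 90%
- equal group sizes (Randomisation and blinding)

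**Step 1. Try to reproduce 48 with the stated settings.**

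n per group = 2 × (z_alpha + z_beta)² × SD² / (true difference − margin)²

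= 2 × (1.960 + 1.282)² × 0.76² / 0.39² = 79.8, so 80. Solving with the noncentral t distribution gives 81. The stated 48 is not reproduced.

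**Step 2. Look for settings that do give 48** (same SD, effect 0.39).

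| Alpha 0.05 | Power | Normal formula | t-based n |
|---|---|---|---|
| two-sided | 90% (as stated) | 79.8 | 81 |
| two-sided | 80% | 59.6 | 61 |
| one-sided | 90% | 65.0 | 66 |
| one-sided | 80% | 46.96 | **48** |

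Only the last row matches, and it differs from the stated settings in both sidedness and power.

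**Step 3. Try the readings without a margin** (two-sided 0.05, 90% power).
- Difference 0.8 against zero: normal formula 18.97, t-based 20 per group.
- Difference 1.19 against zero: normal formula 8.6, t-based 10 per group.

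Neither gives 48.

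**Step 4. Power of the planned size against the margin.**

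The standard error of the difference at 48 per group is 0.76 × √(2/48) = 0.155, and 0.39 / 0.155 = 2.51.
- 48 per group, two-sided 0.05: 71.0% (normal), 70.1% (t).
- 48 per group, one-sided 0.05: 80.8% (normal), 80.3% (t).
- 54 per group (no drop-out), two-sided 0.05: 76.0% (normal), 75.2% (t).

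**Step 5. Difference detectable with 90% power at 48 per group, two-sided 0.05.**

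(1.960 + 1.282) × 0.155 = 0.50 by the normal formula and 0.51 by the t-test. Against the 0.8 margin, the true difference would therefore have to be 0.8 + 0.51 = 1.31, not 1.19.

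**Step 6. Drop-out step.**
- As planned: 48 / 0.9 = 53.3, so 54, and 3 × 54 = 162. Both are correct.
- For the stated 90% two-sided: 80 / 0.9 = 88.9, so 89; 81 / 0.9 = 90. Over three arms this is 267 to 270.

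**The case against.** The strongest objection is that the 70% depends on actually testing against 0.8. The outcome section speaks only of a difference in BCTQ-SSS, and the Analysis plan specifies linear regression without a margin. If the primary test is of zero difference, 48 per group gives over 99.9% power for 0.8 points, and the 30% false-negative risk does not arise. That is right, and the power statement has to be read as conditional on the margin test. It does not rescue the paragraph. The margin test is what the paragraph describes, and under the other reading 20 per group would suffice, so 48 at 90% is wrong there too.

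A second objection is that regression adjusted for baseline BCTQ-SSS would reduce the variance. The article gives no correlation, so any value is an assumption. With r = 0.3 the t-based power at 48 is about 74%, and with r = 0.5 about 82%. Reaching 90% takes r of about 0.63 to 0.64. Moderate adjustment narrows the gap but does not close it, and the paragraph says that the SD of 0.76 is the one used.

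Third, the cause of the error cannot be proved. The match with one-sided 80% is exact only for the t-based formula (the normal formula gives 47), and an SD of about 0.58 would also lead to 48 at the stated settings. This stands: the one-sided 80% setting is a likely explanation, not something the article says. The mismatch itself does not depend on it.

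**Conclusion.** The point holds. With SD 0.76, margin 0.8, true difference 1.19 and the stated "two-sided analysis with a power of 90% (1-β=0.90) at a significant level of α=0.05", the required size is 80 to 81 evaluable per group, not 48. The planned 48 gives about 70% power, and 54 would give about 75%. The shortfall is too large for rounding or choice of formula to explain.

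The power figures assume an unadjusted comparison of two means with a common SD, tested against the 0.8 margin as the section describes. That 48 does not follow from the printed inputs holds with or without the margin. The drop-out inflation and the total of 162 are consistent with 48, so the error is confined to that number and to the power and sidedness attached to it.

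Because it is the central design claim and is false on its own inputs, it should be corrected before the results are reported.

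**What to change.** State which null hypothesis the primary test uses, in both the Sample size calculation and the Analysis plan, and remove the 90% two-sided claim from the 0.8/1.19 inputs. Then use the matching text:

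- **(a) Margin kept.** Suggested text: 48 evaluable participants per group give about 70% power at two-sided 0.05 to show superiority by more than 0.8 points if the true difference is 1.19 (SD 0.76, unadjusted).
- **(b) Null of zero difference.** Suggested text: 48 evaluable participants per group give 90% power at two-sided 0.05 to detect 0.51 points, and over 99% power for 0.8 points (SD 0.76, unadjusted).

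Option (a) follows the section as written. It costs only a less favourable power figure. Option (b) is also a text change, but it gives up the margin and so changes what a positive result means. It has to be a dated decision by the investigators, made without sight of outcomes by group.

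Neither option changes enrolment. Keeping the 90% two-sided claim against the margin on the printed SD and true difference would instead require 89 to 90 enrolled per group, 267 to 270 in all against the planned 162. Correcting the wording does not require that.

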### Analysis plan

Baseline characteristics of the three treatment groups will be summarised using appropriate descriptive statistics. Both the primary and secondary analyses will be blind analyses of treatment assignments and will be performed using the intention-to-treat^55^ method, with all randomised participants retaining their original assigned group. Multiple imputation by chained equations will be used to address missing data caused by lost access and non-response if these missing data are judged to be random.

The primary comparisons for BCTQ-SSS scores will be made using linear regression. In secondary analyses, repeated measures mixed model^56^ will also be used to examine the associations between treatments and repeated outcome measures, with terms of treatment, time, trial centre and corresponding baseline values as covariates (age, gender, body mass index, etc). Bonferroni method will be used to adjust for multiplicity.^57 58^ Linear regression will be used for numerical outcomes, and logistic/ordinal regression for any categorical outcomes.

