**Methods and analysis:**

This study protocol entails a three-arm, prospective, multicentre, randomised controlled trial. 162 eligible adult participants diagnosed with mild to moderate CTS by using criteria developed from a consensus survey by the UK Primary Care Rheumatology Society will be assigned to either (1) therapeutic ultrasound, (2) night splint or (3) therapeutic ultrasound +night splint (combined) group. Primary outcome will be difference in Symptom Severity Scale of Boston Carpal Tunnel Questionnaire (BCTQ-SSS) at 6-week between night splint and therapeutic ultrasound +night splint groups. Secondary outcomes include Functional Status Scale of BCTQ, sleep questionnaire for interrupted sleep, EuroQol-5D for general health, Hospital Anxiety and Depression Scale for mental status, Work Limitations Questionnaire-25 for functional limitations at work, Global Rating of Change for treatment success and recurrence rate, physical examination, electrophysiological and ultrasound parameters. Intention-to-treat analyses will be used.

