### Randomisation and blinding

Participants will be randomised in three intervention groups (either therapeutic US or night splint or therapeutic US+night splint arm) in a ratio of 1:1:1, using a computer-generated randomised sequence with varying unknown block sizes (either 3 or 6) for all study centres, without stratification. A research assistant who are not involved in clinical care and participant evaluations will prepare sequentially numbered, opaque, sealed envelopes based on a random list, and ensure that the allocation data will not be accessed or influenced by anyone. When appropriate, the assistant will open envelopes and ensure coordination of therapeutic interventions.

The outcome assessor and statistician will be blinded to group allocation and not involved in treatment procedures.

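### The primary regression is stated with no covariate, although baseline BCTQ-SSS is collected; naming it in the model would gain precision at almost no cost

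*Protocol article*

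**What the plan says.** The primary contrast is set out in the abstract of the protocol article: BCTQ-SSS "at 6-week between night splint and therapeutic ultrasound +night splint groups". The Analysis plan section gives the method: "The primary comparisons for BCTQ-SSS scores will be made using linear regression". Nothing is said about what else enters that regression, and it is not called unadjusted either.

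The following sentence describes the secondary repeated-measures mixed model and does list its content: "with terms of treatment, time, trial centre and corresponding baseline values as covariates (age, gender, body mass index, etc". The section closes by assigning linear regression to numerical outcomes in general, again without covariates.

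Two other places bear on the point. Data management puts participant assessments at "visits to the hospital at baseline, 6 weeks, 3 months, 6 months and 1 year after random assignment", and Table 1 marks the BCTQ at the enrolment visit. Randomisation and blinding describes one scheme "for all study centres, without stratification", so neither centre nor baseline severity is balanced by design. The Sample size calculation uses an SD of 0.76, taken from the 6-week scores of a published trial, with no reduction for a baseline covariate.

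**The concern.** The baseline value of a symptom score is usually a strong predictor of the same score a few weeks later. Including it removes explained variation from the residual, narrows the confidence interval and corrects for chance differences in starting severity. The plan collects that value, and the authors list covariates for the secondary model but none for the primary one. The raw SD in the sample size calculation also fits an unadjusted primary comparison.

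The secondary model does not settle the matter. Age, gender and body mass index are not baseline values that correspond to an outcome, so the bracket does not explain the phrase it follows. A reader cannot tell whether baseline BCTQ-SSS enters any model, and the list is left open.

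At stake is the width of the primary confidence interval and a covariate set that could be chosen after the data are seen. Validity is not at stake: in a randomised comparison, a regression on treatment alone is unbiased and keeps its type I error rate.

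**Working it through.** **Inputs from the Sample size calculation:** SD 0.76; superiority margin 0.8; assumed true difference 1.19; two-sided alpha 0.05; power 90%; 48 evaluable per group, 54 enrolled.

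**Assumption:** the correlation r between baseline and 6-week BCTQ-SSS is not in the documents. I take 0.3 to 0.6, equal in both arms.

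**Step 1: the plan's own figure.** The distance from the margin is 1.19 − 0.8 = 0.39.

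n per group = 2 × (1.960 + 1.282)² × 0.76² / 0.39² = 79.8, so 80 (81 with the t distribution).

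The stated 48 is not reproduced. It matches one-sided 0.05 with 80% power: 2 × (1.645 + 0.842)² × 0.76² / 0.39² = 47.0, or 48 with the t distribution. The step from 48 to 54 is right (48/0.9 = 53.3, rounded up). The mismatch is a separate matter and does not depend on covariates.

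**Step 2: precision without adjustment.** SE = 0.76 × √(2/48) = 0.155.

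**Step 3: precision with baseline BCTQ-SSS in the model.** The residual SD is 0.76 × √(1 − r²), so SE = 0.155 × √(1 − r²). The variance falls by r², and the equivalent gain in sample size is 1/(1 − r²). Power is for the two-sided test of 1.19 against the 0.8 margin at 48 per group (noncentral t).

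| r | SE | Variance reduction | Sample size equivalent | Power against margin |
|---|---|---|---|---|
| 0 (unadjusted) | 0.155 | – | 1.00 | 70% |
| 0.3 | 0.148 | 9% | 1.10 | 74% |
| 0.5 | 0.134 | 25% | 1.33 | 82% |
| 0.6 | 0.124 | 36% | 1.56 | 87% |

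The normal approximation gives 71%, 75%, 83% and 88%. The degree of freedom spent on the covariate does not alter these figures at the precision shown.

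**Step 4: can adjustment close the gap to 90%?** Ninety per cent at 48 per group needs a residual SD of 0.39 / (3.242 × 0.2041) = 0.589, hence r = √(1 − (0.589/0.76)²) = 0.63. That lies above the assumed range, and the documents offer no figure to support it.

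**Step 5: the zero null.** The Analysis plan does not say that the regression tests against the margin. Against zero, unadjusted, 48 per group has more than 99.9% power for a difference of 0.8, and 90% power for 3.242 × 0.155 = 0.50. Adjustment still narrows the interval in the same proportion but changes power for such differences very little.

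**Step 6: centre.** Suppose, as an illustration, that one of four equal centres differs by 0.3 points. The SD of the between-arm difference in that centre's share is about √(2 × 0.25 × 0.75 / 54) = 0.083. The resulting chance error in the estimate has an SD of about 0.3 × 0.083 = 0.025 points, small beside an SE of 0.155.

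**The case against.** The strongest reply is that a title saying the primary model is unadjusted would rest on silence. Linear regression, unlike a t-test, accommodates covariates. This is a journal article, and the covariate list may sit in a full protocol or SAP that is not shown. That stands: the documents do not say that baseline is omitted. What remains is that the same paragraph spells out covariates for the secondary model and gives none for the primary, and that the list it does give is muddled.

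A reader might also infer that the secondary model leaves out the baseline score. The text does not support that. The word used before the bracket most naturally refers to the baseline value of the outcome being analysed, and a list ending in etc excludes nothing. It is unclear, not wrong.

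A third tempting reading is that missing covariates make the trial underpowered. They do not. The roughly 70% power applies only to the test against the 0.8 margin, and arises because 48 per group does not follow from the stated inputs.

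A fourth is that, with randomisation "for all study centres, without stratification", centre imbalance seriously distorts the primary estimate. Because centre was not a stratification factor, the design does not oblige the analysis to adjust for it. The likely effect, as illustrated above, is small and already covered by the standard error.

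**Conclusion.** The point holds as a matter of precision and clarity. As stated, the primary regression carries no covariate, while baseline BCTQ-SSS is collected and the secondary model lists baseline terms. Leaving the baseline score out would cost precision without causing bias: an SE of 0.155 where 0.148 to 0.124 is attainable if r lies between 0.3 and 0.6. That proportional gain applies under either null. The power gain, from about 70% to between 74% and 87%, applies only to the margin test at a true difference of 1.19. All the gains depend on an assumed correlation, and at the lower end they are modest. Adjustment is no substitute for reconciling the sample size calculation. The case for centre is consistency with the secondary model; its gain cannot be estimated from the documents.

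**What to change.** State the primary model in the Analysis plan as 6-week BCTQ-SSS regressed on treatment group and baseline BCTQ-SSS (continuous), optionally with trial centre to match the secondary model. For the secondary models, name the baseline value of each outcome explicitly, list any further covariates in full, and remove the etc. If a full protocol or SAP already does this, bring the article's wording into line with it. Settle this before unblinding.

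The cost is about one sentence, no new data, and one degree of freedom for baseline BCTQ-SSS (four if the four centres are added).
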